### Statistical methods

The hypotheses tests for the primary and secondary data will be performed on the whole group, and analysis will follow the ITT principle. Data from all sites will be pooled and CI and OR will be estimated for primary outcome (binary), using multi-variable logistic regression models, in line with previous research [29]. Missing data on primary outcome is estimated to be negligible since we use LISA national register data, with below 5% of missingness [79].

Descriptive statistics will be provided to analyse baseline data and help to detect statistically significant differences of interventions group data before allocation. Mixed-effects regression models will be used (secondary outcomes) according to outcome characteristics, time-based (e.g. job-tenure), count-based (e.g. days in employment), binary (e.g. education rate (yes/no), ordinal or longitudinal data if applicable (e.g. health, quality of life and wellbeing outcomes), and proportional-hazard regression (e.g. time to employment) analyses. Repeated measures and time function will be applied in models.

Sensitivity analysis to compare complete data sets and missing data to meet prerequisites for multiple imputations and for co-variety [80]. Sub-analysis will also be performed in relation to intervention site (random), gender, age and alcohol and drug use. Alpha will be set at 5% with associated 95% CIs. Statisticians from the Unit of Medical Statistics and Epidemiology, Clinical Studies Sweden-South Forum, Skånes University Care are consulted to produce a more detailed plan to be published before analysis. Primary data will only be available to researchers in the present trial.

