### Outcomes

Assessment of primary, secondary, and other self-reported outcomes is done at baseline (-*t*^1^), before allocation, and at 6–12–18 months (*t*^1^–*t*^3^) (Table 1). Vocational primary and secondary outcomes will be retrieved retrospectively (> 18 months), via Statistics of Sweden from the LISA register data base (Swedish Longitudinal Integrated Database for Health Insurance and Labour Market Studies) [57]. Secondary and other self-reported variables are reported in an online RedCap system [58]. Adverse Events will be collected continuously.

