### Sample size

The primary outcome is used to calculate the required sample size to detect a significant mean difference between the intervention groups at 18 months follow-up (employment rate, yes/no). No previous trial has been published within the field of AS, why the estimation is done against previous IPS trials. According to Marsden et al. [28], using a DELTA^2^ guidance based a meta-analysis from 2019 [18], 302 participants were deemed to be a sufficient sample size (95% CI). When departing in previous Swedish high-fidelity IPS trials, targeting persons with psychosis [20] and depression [22], power calculations (Fisher’s exact test) show the required sample size of 60 and 40 respectively to detect a power of 80% and alpha level at 0.05 (95% CI). One point of departure for aiming at a larger sample size than previous trials is that the dropout rate for persons in AS is assessed to be equivalent or even larger than for those with mental health problems, according to the attendance rates in similar interventions within AS in one of our trial contexts (City of Stockholm). A rate of ≥ 30% drop-out must therefore be considered. Another point of departure regards the criticality to detect statistical a mean difference for secondary outcomes (e.g. ordinal data) which according to a meta-study needs to increase in IPS trials, overall [78]. Lastly, the employment specialists typically have a caseload of a maximum of 20. But since their capacity to support persons with addiction is unknown, the number of maximum participants we estimate to be 15. In all, we intend to involve 9 employment specialists (Stockholm, *n* = 5; Södertälje, *n* = 3, Lund/Malmö, *n* = 3). As a suggestion, the ambition is to include a total of approx. 165 + 165 participants, a total of 330, Stockholm (*n* = 150) and Södertälje (*n* = 90) (East Middle Sweden) and Malmö/Lund (*n* = 90) (Southern Sweden). Distribution of the participants between the locations may be adjusted in accordance with recruitment rates at each site.

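### The one missing-data sensitivity analysis named for the trial cannot establish missing at random and varies no assumption, although the questionnaire models depend on that assumption

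*Protocol article*

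**What the plan says.** All of this is in the protocol article.

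- **Missing-data check (Statistical methods).** The only sensitivity analysis named for missing data is "Sensitivity analysis to compare complete data sets and missing data to meet prerequisites for multiple imputations"; the sentence then adds a reference to covariates.
- **Main analysis of secondary outcomes (same section).** "Mixed-effects regression models will be used (secondary outcomes) according to outcome characteristics", and "Repeated measures and time function will be applied in models".
- **Source of these outcomes (Outcomes).** "Secondary and other self-reported variables are reported in an online RedCap system". Health, quality of life and well-being are collected this way at baseline and at 6, 12 and 18 months.
- **Expected loss (Sample size).** A rate of at least "30% drop-out must therefore be considered", justified by attendance in similar interventions at one of the trial's locations.
- **Register data (Statistical methods; Data collection and management).** Employment, income and benefit data come from LISA. For the primary outcome, missingness is called negligible "since we use LISA national register data, with below 5% of missingness".
- **Contact by arm (Guidance for discontinuing interventions and promotion of adherence).** IPS includes continuing support and outreach to keep in touch. The TVR arm has no overall guidance of this kind; each welfare agency follows adherence within its own step.
- **Detail to come (Statistical methods).** A fuller analysis plan is to be published before analysis.

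**The concern.** Multiple imputation in its standard form, and a likelihood-based mixed model, both assume that missingness depends only on what the model has observed. Comparing people with and without complete data can refute the stronger assumption of missing completely at random. It cannot confirm missing at random, because that assumption concerns the values nobody saw. If the comparison finds differences, that is no reason to withhold imputation. If it finds none, that is no evidence that imputation is safe. Nor is it a sensitivity analysis in the usual sense, since no assumption is changed and no treatment contrast is re-estimated.

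The second research question, on health, quality of life and well-being, rests on self-report. The protocol regards work as a likely route to better health, and the trial aims to make employment differ by arm. If having a job also affects whether people answer, and does so differently in the two arms, the arm contrast can shift without the comparison revealing it.

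**Working it through.** No figure in the plan can be reproduced here, because the point concerns an assumption. The steps below show what the check can and cannot do, then the possible size.

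**1. What the documents fix.** N = 330, 165 per arm. At 30% loss, 0.70 × 330 = 231 respond (115.5 per arm) and 99 do not. With register missingness below 5%, at most 0.05 × 330 = 16.5 people lack register data. Even if all of them were among the 99, about 82 non-responders would still have it.

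**2. Precision at 231 responders** (80% power; 5% alpha taken as two-sided).
- SE = √(2/115.5) = 0.132 SD.
- Detectable difference = 2.80 × 0.132 = 0.37 SD, against 0.31 SD with all 330.

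**3. Bias if response depends on employment.** All inputs are assumptions; the documents give none. Employment is 25% (TVR) and 40% (IPS), and employed people score 0.5 SD better. The true contrast is 0.5 × (0.40 − 0.25) = 0.075 SD. With employment share p and response rates r_e (employed) and r_u (not employed), the employed share among responders is p·r_e / [p·r_e + (1 − p)·r_u]. The estimate is 0.5 × the difference in those shares.

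| Response, employed/not employed | TVR share | IPS share | Estimate (SD) | Bias (SD) |
|---|---|---|---|---|
| TVR 80%/55%; IPS 75%/75% | 0.2000/0.6125 = 0.327 | 0.400 | 0.037 | −0.038 |
| TVR 65%/72%; IPS 85%/65% | 0.1625/0.7025 = 0.231 | 0.340/0.730 = 0.466 | 0.117 | +0.042 |
| Both arms 80%/55% | 0.327 | 0.320/0.650 = 0.492 | 0.083 | +0.008 |
| Both arms 85%/65% | 0.2125/0.7000 = 0.304 | 0.466 | 0.081 | +0.006 |
| Both arms 65%/72% | 0.231 | 0.260/0.692 = 0.376 | 0.072 | −0.003 |

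The calculation takes one time point and ignores earlier scores. A repeated-measures model would usually recover part of the loss.

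**4. Simulation** (2,000 runs, N = 330; assumed employment 20% in TVR and 40% in IPS, true difference 0.10). With a sharper reversal between arms (non-response 5%/40% in IPS and 40%/30% in TVR, employed/not employed), the available-data model without employment gave 0.17. Imputation using register employment gave 0.10. With the same mechanism in both arms the results were 0.11 and 0.10.

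**5. What the comparison would show.** In the same simulation, a 5% test of baseline score between responders and non-responders was positive in 4% to 5% of runs in every scenario, including one where missingness depended on the unseen outcome. That is the false-alarm rate. Missingness was built to be unrelated to the baseline score, so this shows that the check can stay silent, not that it always will.

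**6. Departures that register data do not capture.** Bias = missing share × the difference between arms in the unmodelled shift. At 30% missing, a 0.5 SD shift in one arm only gives 0.30 × 0.5 = 0.15 SD. A result equal to the detectable difference would lose significance at a one-arm shift of (0.369 − 1.96 × 0.132)/0.30 = 0.37 SD. This last figure follows from the sample size and missing share alone. It does not measure harm done by the quoted sentence.

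**The case against.** The strongest reply is that the check matters little. The questionnaire outcomes have a main analysis, the mixed model with repeated measures, which uses every observed wave and is valid under missing at random without imputation. A reader might infer that these outcomes rest on the complete-versus-missing comparison; they do not. This stands.

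A reader might also infer that the register data will go unused for these outcomes. The article does not say so. It lists no imputation variables or covariates and defers detail to a later plan, so their absence here is not an error. This stands too.

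The 30% is drawn from intervention attendance, not questionnaire response. Everyone is followed unless they withdraw, with reminders, paper forms and personal help in both arms, so 231 responders is a planning illustration and not a forecast. The quoted sentence is also grammatically incomplete and gives no test, threshold or consequence. It may mean no more than describing missingness and finding predictors of it, so reading it as a formal pass/fail rule goes beyond the text.

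Finally, the illustrated biases look large as proportions only because the assumed contrast is small. In absolute terms, 0.04 SD is about 0.3 of the standard error and one-ninth of the detectable difference.

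None of this makes the comparison capable of meeting the prerequisite that it is said to meet, or turns it into an analysis that varies the missing-data assumption.

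**Conclusion.** The point holds in a limited form. The one missing-data sensitivity analysis that the article names cannot do what it is named for, and the mixed models share the assumption that it leaves untested. The arms differ in the contact support described, so differential response is plausible, but the documents do not show that it will occur.

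The expected size is modest: about 0.04 SD if response depends on employment differently by arm, 0.07 SD under the sharper pattern simulated, and under 0.01 SD in the closed-form cases with the same pattern in both arms. These figures rest on assumed employment rates, response rates and a 0.5 SD effect of work. Larger bias needs departures that register data cannot explain, such as non-response driven by relapse. The primary outcome comes from the register and is unaffected. This is an inexpensive improvement for secondary outcomes, to be settled before analysis.

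**What to change.** In the detailed analysis plan:

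1. Keep the comparison of complete and incomplete records as description only, not as a condition for imputation.
2. Keep the mixed model as the main analysis of the questionnaire outcomes and state that it assumes missing at random.
3. As the sensitivity analysis, impute questionnaire outcomes separately by arm, using baseline and earlier scores plus LISA employment, income and benefit variables as auxiliaries.
4. Apply a pre-specified delta adjustment per arm to the 18-month contrast (for example 0 to −0.5 SD for non-responders) and report the tipping point.

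Two matters need confirming first. One is person-level linkage of register and questionnaire data: the Data collection and management section describes the register data both as anonymised and as pseudonymised. The other is the time resolution that the register delivers, since it is updated annually and may not align with the 6-, 12- and 18-month waves. The figure of below 5% missing is given for the primary outcome and should be checked for income and benefits.

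The cost is plan wording, some programming and the linkage check. No new data collection is needed. Step 4 is needed as well as step 3, because register variables help only where employment, income or benefits explain non-response.

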### Monitoring

The PI will have overall responsibility for data and will be supported by the research coordinator who is hired for the trial for independent monitoring and auditing trial conduct. The coordinator will further organise and integrate monitoring with an external trial reference group (meets quarterly), a trial management group (meets biweekly). Additionally, operational work groups will be developed at each site to coproduce any solution for IPS implementation and trial (meets weekly). The Ethics Committee is not part of the auditing trial conduct.

Steps and passages of the trial, e.g. recruitment, enrolment, quality of data, analysis, safety, harms and unintended effects of the interventions or trial conduct will be monitored and communicated. A report of the progression of the trial will be conducted by the trial management group and conclude significant benefits and risks (= 1 year since enrolment). No interim results of data will be performed. The trial steering and management group will involve members from the AS who deliver the intervention, as well as public and user involvement organisations. No data monitoring committee is appointed by the trial sponsor (FORTE) but monitors the trial online via the administrative research system of PRISMA (https://prisma.research.se/. The sponsor requires updates annually, a brief report on the progression of the trial by halftime, while a thorough report of advancements and results is presented post-trial. The PI is responsible for these activities together with the Head of the Department of Health Sciences and the chief economist.

Data and safety measures will further be covered by monitoring groups mentioned and experienced research administrators and statisticians. In addition, unforeseen events and harms (Adverse Events, AE) among participants will be continuously observed and recorded in a special document (AE form) and be instantly reported by the trial management group to the trial steering committee and PI. These events may include suicide attempts and hospitalisation, for example.

### Dissemination plans

Trial results will be disseminated to AS providers, service users, service user organisations and the public by means of peer-reviewed scientific journal publications and popular reports written so that all participants can share the results. Since the present trial is performed in coproduction, any party may share their learning with others. Workshops with stakeholders and service users will also be held if the IPS-ADAS trial is beneficial and further implemented. All scientific publications will have open access and results will further be disseminated in national and international conferences and research networks. Authors will conform to the guidelines of ICMJE (https://www.icmje.org/) when conducting, editing, and publishing in medical journals.

## Discussion

A primary study on the effectiveness of IPS on employment for the new target group and within a new field of practice. Results will further add to the international IPS knowledge base and inform national policy to include an underrepresented group of addictions into working life. To our knowledge, the IPS-ADAS will be the first RCT to investigate the effectiveness of IPS in Sweden. Thus, this study will provide important information about the effectiveness of IPS in employment, health, quality of life and well-being for a new target. It will also deepen our understanding of the complex situation that many of these people find themselves in, a group who find themselves in great need of hope and support to develop a work identity and finding a job. Our partnership with user organisations and AS providers will further provide knowledge and clarity of how coproduction efforts may enhance the implementation of IPS and optimise the quality of the trial and to build capacity and work culture to engage in future research. Coproduction will combine experienced knowledge from all stakeholders, including researchers, and is presumed to reinforce recovery-oriented knowledge into practice that matters for service users.

Positive results could also justify IPS as an evidence-based intervention to be used routinely for persons with addiction in Sweden, and in this case, expected to be used more frequently and be offered as a critical ingredient in future innovations within Addiction service and treatment. To provide opportunities for work and health early in the life course is also a critical shift for proactive ageing [81].

## Trial status

This is the 1.1 protocol of the trial which will be submitted to the BMC Trial on 3 November 2023. The overall start date of the planning and application of Ethical approval was 1 September 2022, and the end date of data collection is planned for 30 June 2026. Recruitment of the first AS site was on 15 January 2023. The start date for recruitment of participants was on 1 September 2023, in tandem with approval and receipt of research funding (FORTE, register number 2023–00080) and registration of the IPS-ADAS trial at the WHO International Clinical Trials Registry Platform on 14 August 2023, with the trial register number ISRCTN10492363. Recruitment will end on 28 February 2025. Updates and modifications of the trial will be updated.

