### Participant timeline

Enrolment begins when presumptive study participants gain brief written and verbal information about the IPS-ADAS trial from professionals within the AS (Fig. 1). Once inclusion and exclusion criteria are broadly met (pre-screening), interested persons are invited to partake in an information/dialogue meeting (group/individually) to understand eligibility and the meaning of participating in the trial more fully, before signing their written consent (30–45 min). Their written consent may also be handed in afterwards. In connection to enrolment, baseline data is contained (questionnaire battery, 30–50 min) after which allocation to one of the two interventions (IPS + TAU and TVR + TAU) is performed. Participants will attend the interventions for 12 months. The questionnaire battery is repeated at 6 (168 days), 12 (365 days) and 18 months after the randomisation date, with a 21-day window after the due date at the 6- and 12-month follow-up, and 28 days at 18 months.

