### Recruitment, allocation, and blinding

For each site, enrolment will last for about 18 months, from September 2023 to February 2025. Healthcare professionals from AS will assist to identify eligible participants by reviewing health records and approaching users and screening will last until the population of the target is reached for each site. Verbal information will further be advertised in waiting rooms and on social media of research- and user organisations targeting the group of interest. In connection with this initial recruitment phase, it will also be possible for presumptive users to self-register and pose their interest at a website whereupon they are referred to healthcare professionals for brief oral and written information about eligibility.

If criteria are met, presumptive users will be invited to partake in an information meeting (group or individually) at their site. The meeting will target the interventions as well as issues around the RCT design, randomisation, and ethical approval. The content and delivery of the information meetings will follow a premade protocol description and meetings will be held by a healthcare professional and researchers, a research administrator, and a user representative with lived experience of addiction and re-entering employment. Family and friends of presumptive participants may also partake for support. The aim is to provide democratic spaces to inform eligible users and openly discuss the project. Individual meetings may be held by a healthcare professional or a researcher. Any time after attending the meeting users may hand in their written consent. The duration of the recruitment will be approximately 1 year for each site respectively.

After completion of baseline assessment, participants will be randomly assigned to one of the two intervention arms (ratio 1:1) using randomly varying block sizes, using a randomisation schedule automatically generated in RedCap to assure allocation concealment, with no stratification. A randomization list (Excel file) will be kept separate and be administrated by a research administrator who will manage the allocation sequence, enrollment of participants, and assignment to interventions by sending a standardised letter about the IPS + TAU and TVR + TAU intervention respectively by mail, within a week.

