### Data collection and management

Researchers will retrieve anonymised primary and secondary vocational, income and benefit data from the LISA database in which data from the labour market, social and educational sector is integrated and updated annually, focusing on the individual as the primary object. Data will be retrieved by Statistics Sweden and the procedure is that the research assistant will submit personal security number data with a variable order to Statistics Sweden which they co-run and deliver back to the researchers pseudonymised. In addition, vocational data will be registered by the participants in connection to RedCap data collection (ASI).

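### Data collection is planned to end about two months before the last recruits' 18-month assessment is due, and about three before its window closes

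*Protocol article*

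**What the plan says.** The Trial status section of the protocol article gives three calendar dates: "The start date for recruitment of participants was on 1 September 2023", "Recruitment will end on 28 February 2025", and "the end date of data collection is planned for 30 June 2026". The section on recruitment, allocation and blinding agrees on the recruitment period: "For each site, enrolment will last for about 18 months, from September 2023 to February 2025".

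Follow-up is counted from randomisation. The Participant timeline section states: "The questionnaire battery is repeated at 6 (168 days), 12 (365 days) and 18 months after the randomisation date". It then allows 21 days after the due date for the 6- and 12-month assessments and 28 days for the 18-month assessment.

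The Outcomes section separates two data sources. The primary and other vocational outcomes come from the LISA register and are to be fetched retrospectively, beyond 18 months. The other secondary outcomes are self-reported in RedCap. The Primary outcome subsection adds that the register data will be checked against the employment status participants report in the ASI and against the employment specialists' logbooks.

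**The concern.** The interval from the end of recruitment to the end of data collection is shorter than the follow-up that every participant is meant to complete. The Objectives section names 18 months as the comparison time for employment, addiction, care use, health, quality of life and well-being. A fixed stop on 30 June 2026 would therefore remove the main time point for the self-reported outcomes in everyone recruited late.

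This loss would add to ordinary attrition. The Sample size section already allows for dropout of 30% or more, and it gives detection of differences on secondary outcomes as one reason for the larger sample. The stated end date works against that reason. It would also remove the 18-month ASI employment answers for late recruits, and with them part of the planned validation of the primary outcome.

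**Working it through.** **Inputs**
- Recruitment: 1 September 2023 to 28 February 2025 (Trial status).
- End of data collection: 30 June 2026 (Trial status).
- Final assessment: 18 months after randomisation, window 28 days (Participant timeline).
- Sample size: 330 (Trial design).

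**Follow-up available to the last recruit**
- 28 February 2025 to 28 February 2026 is 365 days, and on to 30 June 2026 is 122 more. The total is 487 days, or 487 / 30.4375 = 16.0 months.

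**Follow-up required**
- Due date: 28 February 2025 + 18 months = 28 August 2026, which is 31 + 28 = 59 days after 30 June 2026.
- Window closes: 28 August 2026 + 28 days = 25 September 2026, which is 59 + 28 = 87 days after 30 June 2026.

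**Other readings of 18 months**

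The protocol counts 6 months as 168 days and 12 months as 365 days but gives no day count for 18 months, so several were tried from 28 February 2025.

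| Reading | Due date, days after 30 June 2026 | Window close, days after 30 June 2026 |
|---|---|---|
| 18 calendar months | 59 | 87 |
| 548 days | 61 | 89 |
| 365 + 168 = 533 days | 46 | 74 |
| 3 × 168 = 504 days | 17 | 45 |
| Randomised 7 days after recruitment closes, 18 calendar months | 69 | 97 |

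Every reading ends after 30 June 2026.

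**Number affected, assuming uniform accrual**

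Recruitment covers 547 days, counting both ends.
- 18 months not reached by 30 June 2026: randomised 1 January to 28 February 2025, 31 + 28 = 59 days. 59 / 547 = 10.8%, and 0.108 × 330 is about 36.
- Full 28-day window not available: randomised 3 December 2024 to 28 February 2025, 29 + 31 + 28 = 88 days. 88 / 547 = 16.1%, and 0.161 × 330 is about 53.

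**Range under other accrual patterns (assumptions)**
- If every site filled within one year of 1 September 2023, the last recruit would enter by 31 August 2024 and nobody would be affected.
- If accrual were uniform over only the last 365 days to 28 February 2025, the counts would be 59 / 365 × 330 = about 53 and 88 / 365 × 330 = about 80.

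**Effect on 18-month responders (assumption: 30% non-response, independent of recruitment date)**
- Without the early stop: 0.70 × 330 = 231.
- With it: 231 × 488 / 547 = about 206, or 231 × 459 / 547 = about 194 if nobody without a full window responds.

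**The case against.** The strongest objection concerns the primary outcome. A reader might infer that late recruits would be counted as not employed over a shortened period, so that the primary comparison is truncated. The document does not support that as the plan. The Outcomes section says the vocational data are fetched from the register retrospectively, beyond 18 months, and the Statistical methods section expects under 5% missing. A later extract can cover 18 months for everyone without contacting anyone. An extract by 30 June 2026 would itself conflict with the Outcomes section for late recruits. This objection stands. What remains is a conditional risk, because the Trial status section does not exempt register data from its end date.

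A reader might also note that the register is "integrated and updated annually" and infer that a mid-2026 extract would lack recent employment for a large share of the sample. That needs an extraction date and a register lag, and the document gives neither, so no figure is offered.

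The counts of 36 and 53 rest on uniform accrual. Screening at each site stops when its target is reached, so early filling would reduce them and slow early accrual would raise them. This stands and is why a range is shown.

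The section on recruitment also says: "The duration of the recruitment will be approximately 1 year for each site respectively". A reader might take this as removing the conflict. It does not, because the same section and the Trial status section both put the end of recruitment in February 2025. The disagreement between one year and about 18 months per site is a separate drafting point.

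Finally, the end date is described as planned and open to updating. Allocation is 1:1 in varying blocks, so the loss would fall roughly equally on the two arms. Both points limit the harm, which is mainly to completeness and precision, but neither makes the dates agree.

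**Conclusion.** The stated dates are incompatible. With recruitment to 28 February 2025, the last 18-month assessment falls due about two months after the planned end of data collection, and its window closes about three months after. This follows from printed dates alone, and no reading of 18 months removes it.

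The consequence depends on the date being applied as written. In that case about 36 of 330 participants (11%), or about 53 (16%) counting the full window, lose their 18-month self-reported outcomes and the ASI employment answers used for validation. Those counts assume uniform accrual; the alternative patterns tried run from none to about 53 and about 80 respectively. Truncation of the register-based primary outcome is not established. It would follow only if the extraction were also tied to 30 June 2026.

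**What to change.** Move the end of data collection to at least 25 September 2026. It is better stated as a rule: last randomisation plus 18 months plus 28 days. If randomisation of the last participant slips a week past the close of recruitment, the rule gives 5 October 2026. Time the register extraction so that it covers 18 months from each participant's own randomisation date, and say so.

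Keeping 30 June 2026 would instead require the last randomisation by about 2 December 2024 with the full window (2 December 2024 + 18 months + 28 days = 30 June 2026), or by about 31 December 2024 with no window. That shortens recruitment and is unnecessary if the end date can move.

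The cost is a date amendment and later results: about three months for the questionnaires, and for the register whatever its annual update requires. No extra participants are needed, and the design and analysis do not change.
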